**Perceived Stress Scale (PSS):** The PSS (39) is a widely used instrument for measuring individuals’ perceived stress. It assesses how much our daily situations are perceived as stressful, unpredictable, and ultimately overloading. Moreover, the PSS also assess the current level of perceived stress directly, providing a reliable and robust instrument for stress assessment. Items in the PSS assess feelings and thoughts the last month, however the scale will be adapted to assess perceived stress in the last week. The instrument is composed by 10 items on a 5-point Likert A composite score of the 10 items provide a general measure of perceived stress.**Depression Anxiety Stress Scale (DASS-21):** The DASS-21 (40) is a short version of the original instrument developed by Lovibond and it is composed of 21 items divided into 3 subscales that measure anxiety, depression, and perceived stress. The scale assesses how the participants felt in the previous 7 days on a 4-point Likert. Scores are computed individually for each subscale. A composite score of general distress is obtained by computing all the three subscale scores together.**Beck Hopelessness Scale (BHS):** The BHS (41) is a self-report instrument that measures pessimistic tendencies or negative attitude towards the future within three major aspects of hopelessness: feelings about the future, loss of motivation, and expectations. The scale is composed of 20 items with a True/False response.**Social Connectedness Scale (SCS):** The SCS (42) is composed of 8-items and aims at measuring how much the individual feels connected to other persons or to the social context. The scale asks to evaluate agreement or disagreement to several contextual statements on a 6-point Likert scale. Higher scores represent a higher sense of social connectedness.**Fear of Coronavirus (FCOR):** FCOR is a series of statements presented in (43) to measure the level of fear toward the COVID-19 pandemic. FCOR is composed of 8 items that explore different components of fear such as the personal experience of concern regarding the current situation, avoidance behaviors and attention bias. Each statement is evaluated on a 5-point Likert.**Online and offline contact (COO):** COO is a series of questions (44) to measure the number and quality of online and offline contacts during the COVID-19 pandemic. Individuals are asked to report the number of online contacts in the past week evaluating on a 5-point likert scale how close they felt to those contacts. The same two questions are repeated for offline contacts.

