
#### State Measures Collected From Day 1 to Day 7

**Smith Relaxation State Inventory 3 (SRSI3):** The SRSI3 (45) is the revised form of the original Smith Relaxation State inventory and it measures both relaxation and perceived stresses. Individuals rate their agreement to several statements on a 6-point Likert scale. The scale is composed of 38 items; however, it is divided into several subscales that can be selected independently. For this protocol, the following subscales have been selected, for a total of 20 items: rest/refresh, energized, physical relaxation, at ease/peace, joy, mental quiet, aware, somatic stress, emotional stress, and cognitive stress.**Subjective Units of Distress Scale (SUDS):** The SUDS (46) is simple numeric rating scale from 0 to 100 that measures the level of distress perceived by the individual. It is a reliable measure of state distress, commonly used in cognitive behavioral therapy.

#### Post Intervention Measure Collected at Day 7

**Negative Effects Questionnaire (NEQ):** The self-report measure consists of three parts for a total of 32 items (47). First, respondents endorse specific items in case they have occurred or not during treatment, yes/no (dummy coded as a variable: 1/0). Second, the respondents rate how negatively the negative effect was on four-point Likert-scale, ranging from “Not at all” to “Extremely”, 0–4 (“0” being minimum and “4” being maximum). Third, the respondents attribute the negative effect to “The treatment I received” (1) or “Other circumstances” (0) (dummy coded as a variable: 1/0).**Simulation Sickness Questionnaire (SSQ):** The self-report measure is composed by 16 items used to users’ level of sickness symptoms after a VR experience (48).**Final Interview:** This final interview aims at collecting any additional information related to practical challenges of using the VR app and coordinating the self-help social task.

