### Outcomes

Considering the presented hypotheses, the primary outcomes expected for the group that will perform the experimental VR procedure compared to the control group are:

A reduction in anxiety, depression, perceived stress, and hopelessness, as measured by DASS-21, PSS, and BHS.A reduction in state anxiety and subjective distress, as measured by SUDS.And an increase in relaxation, as measured by SRSI3.

Secondary outcomes of the protocol are

a decrease in fear of the coronavirus, as measured by FCOR;an increase in social connectedness, as measured by SCS;an increase in feelings of closeness to online and offline contacts, as measured by COO.

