## Statistical Analysis

Categorical variables will be compared using Fisher or chi-square tests and continuous variables using t test or Mann-Whitney tests, as appropriate. Groups will be compared for variables such as sex, age, education, geographic area, stage of disease, type of proposed treatment, and other available data. To assess the effectiveness of the intervention, groups will be compared with a 2 × 2 repeated measure mixed ANOVA for the pre and post measures (factor Group X factor Time: pre and post). Analysis will be performed for all the relevant variables: perceive stress, anxiety, depression, hopelessness, fear of the coronavirus, and social contacts. A repeated measures ANOVA (factor Group × factor Time: day of the week) will compare treatment effects within the seven-day intervention, for all the relevant measures: relaxation, perceived stress, and state anxiety. Tests of statistical significance and confidence intervals will be two-sided; a p < 0.05 will be considered to be statistically significant. Statistical computations and data analysis will be performed using R, a multi-platform (Windows, UNIX, Mac OS), free software environment for statistical computing and graphics.

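### About seven co-equal primary outcomes are each judged at an unadjusted two-sided 0.05, with no rule on how many must succeed and a sample size that covers one test

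*Protocol article*

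**What the plan says.** The Outcomes section lists three primary items without ranking them:

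- "A reduction in anxiety, depression, perceived stress, and hopelessness, as measured by DASS-21, PSS, and BHS"
- "A reduction in state anxiety and subjective distress, as measured by SUDS"
- "And an increase in relaxation, as measured by SRSI3"

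Under Psychological Measures, the DASS-21 yields three subscale scores ("Scores are computed individually for each subscale"). A composite is also described ("A composite score of general distress is obtained by computing all the three subscale scores together"), but the Outcomes section does not list it. Ten SRSI3 subscales are selected: "rest/refresh, energized, physical relaxation, at ease/peace, joy, mental quiet, aware, somatic stress, emotional stress, and cognitive stress". The article does not say whether relaxation will be one score or several.

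The Statistical Analysis section plans a 2 × 2 mixed ANOVA (Group × Time) for the pre/post scales and a repeated measures ANOVA over the seven days for the daily scales. For all of them, "Tests of statistical significance and confidence intervals will be two-sided" and "a p < 0.05 will be considered to be statistically significant". It states no hierarchy, correction or success rule.

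The Power Size Calculation section gives f = 0.25, alpha 0.05, two groups, power 0.95 and a total of 54.

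**The concern.** When several outcomes share primary status and each has its own 5% threshold, the trial has several chances to produce a positive primary result. With no rule on how many must succeed, the reader of the final report cannot tell what a success means. One significant score out of seven could be presented as evidence that the protocol works, and the chance of that happening without any effect is well above 5%.

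The sample size is affected as well. It was set for one test at 0.05. If the outcomes are adjusted for multiplicity, or if all of them must succeed, the quoted 0.95 does not describe the trial's power.

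**Working it through.** **Inputs from the article.** Per-test alpha 0.05, two-sided; f = 0.25; two groups, 1:1; two time points in the pre/post model; stated N = 54; at least 30 per arm in each research group, with three countries named. **Assumed.** Correlation between outcomes (range shown) and pre/post correlation 0.5. The article gives neither.

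**1. The plan's own figure.** For the Group × Time interaction with m = 2 measurements, the noncentrality is λ = f² × N × m / (1 − ρ), with 1 and N − 2 degrees of freedom.

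- N = 54, ρ = 0.5: λ = 0.0625 × 54 × 2 / 0.5 = 13.5, power 0.950.

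So 54 reproduces for one unadjusted pre/post interaction test. A test of the between-group factor would need 158 and a one-way comparison 210, so the interaction is the reading that fits.

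**2. Number of primary tests.**

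- DASS-21 (3) + PSS (1) + BHS (1) + SUDS (1) + SRSI3 relaxation (1) = 7.
- The constructs in the Statistical Analysis section also give 7: stress, anxiety, depression and hopelessness pre/post, plus relaxation, stress and state anxiety daily.
- If PSS and DASS-21 stress are treated as one construct, the count is 6.
- If the seven relaxation-type SRSI3 subscales were tested separately, it would be 6 + 7 = 13. The three stress subscales are not part of an outcome defined as more relaxation.

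**3. Chance of at least one false positive when there is no effect.**

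- Independent outcomes, either direction: 1 − 0.95^k. For k = 7: 1 − 0.698 = 0.302.
- Independent outcomes, favouring VR only: 1 − 0.975^k. For k = 7: 1 − 0.838 = 0.162.
- Equal correlation r: one minus the integral over x of φ(x) × [Φ((c − √r·x)/√(1−r)) − Φ((−c − √r·x)/√(1−r))]^k, with c = 1.96. Dropping the second Φ term gives the favourable direction only.

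| Tests | Direction | r = 0 | r = 0.5 | r = 0.7 | r = 0.8 |
|---|---|---|---|---|---|
| 7 | either (one test: 5%) | 30.2% | 23.0% | 17.8% | 14.9% |
| 7 | favouring VR (one test: 2.5%) | 16.2% | 11.5% | 8.9% | 7.4% |
| 6 | either | 26.5% | 20.7% | 16.4% | 13.9% |
| 13 | either | 48.7% | 33.4% | 24.1% | 19.2% |

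The normal model is only approximate for the daily ANOVA, whose F tests have several degrees of freedom.

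**4. Power at the strictest Holm step for seven outcomes.** Alpha = 0.05 / 7 = 0.0071, same formula, ρ = 0.5.

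| N | λ | Power at 0.05 | Power at 0.0071 |
|---|---|---|---|
| 54 | 13.5 | 95.0% | 80.4% |
| 60 (one research group) | 15 | 96.8% | 85.6% |
| 180 (3 × 60) | 45 | > 99.9% | > 99.9% |

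A total of 80 restores 95% at the strictest step. Later Holm steps use larger alphas, so these are worst cases. They apply to the pre/post outcomes; the article gives no power calculation for the daily ones.

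**The case against.** **The article states no any-one-suffices rule.** This stands. The Hypotheses section joins depression, anxiety, stress and hopelessness in one sentence, which could mean that all must improve. If all were required, alpha would need no adjustment, but the chance that every test succeeds would be below 0.95: with seven independent tests each at 0.95 power, 0.95^7 = 0.70, and more if the outcomes are correlated. The figures in step 3 therefore depend on the any-one reading, which the article neither adopts nor excludes.

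**A reader might infer sixteen primary tests and an error rate of 56%.** The text does not support this. Sixteen includes the three SRSI3 stress subscales, which lie outside the stated outcome. Testing by subscale is never announced, and 56% further requires independence among subscales of the same instrument.

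**A reader might also infer that 5% and 0.95 hold for none of the trial's claims.** That is too strong. Each single test keeps its 5%, and N = 54 is right for one pre/post interaction under the assumed correlation.

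**Two-sided figures count results against VR.** This is correct, since the outcomes are directional. The favourable-direction figures are about half as large, but they are still roughly three to six times their 2.5% benchmark.

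**This is a pilot, and an unseen analysis plan may handle multiplicity.** The pilot label lowers the stakes, and the Abstract does mention feasibility. But the Aims seek evidence that the protocol helps, the analysis is said to assess effectiveness, and the trial is powered at 0.95 for an effect. The choice of several equal primary outcomes and their threshold is made in this article. A later correction would have to change that rule.

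**Conclusion.** The concern holds as a problem of undefined success among co-equal primary outcomes. With seven tests at 0.05 and the any-one reading, the chance of at least one false positive under no effect is about 15% to 30% (correlation 0.8 to 0), or about 7% to 16% for results favouring VR against 2.5%. Six tests give slightly less; separate testing of the relaxation subscales gives more. The correlations are assumptions, but every case computed is well above the single-test rate.

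The sample size is not miscalculated. It applies to one unadjusted pre/post test, and the article does not say which outcome that test concerns.

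**What to change.** Amend the Outcomes and Statistical Analysis sections before outcome data are seen:

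1. Define one SRSI3 relaxation score, and report the remaining SRSI3 subscales as estimates with confidence intervals only.
2. Choose one of two routes. (a) Keep the listed primary outcomes and test each Group × Time effect by Holm at a familywise two-sided 0.05. (b) Name one listed outcome as sole primary at two-sided 0.05 and test the others as a Holm-adjusted secondary family.
3. State what counts as success of the trial.
4. State in the Power Size Calculation section that 0.95 at 54 refers to one unadjusted pre/post test. Under route (a), add the strictest-step figures and the assumed pre/post correlation.

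Making the DASS-21 composite the sole primary is possible but debatable, because it is not among the listed outcomes and the choice would demote hopelessness, distress and relaxation.

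The cost is a text change with no new data collection. Fewer outcomes may be called significant. Under route (a), worst-case pre/post power falls from about 97% to 86% at 60 participants, with almost no loss at 180.

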## Power Size Calculation

Power size calculation was performed with GPower 3.1. Considering an anticipated effect size (f) of.25, an alpha set at.05, 2 groups, and a.95 statistical power, the total sample size required is N = 54.

## Discussion

Living in the time of the coronavirus means experiencing not only a global health emergency but also extreme psychological stress that puts a strain on our identity and our relationships. The fears about personal health and the health of friends and family members, and the effects of the quarantine generate significant psychological effects including post-traumatic stress symptoms, depression confusion, and anger. These negative psychological effects may be enhanced by other stressors such as having inadequate basic supplies (i.e., food, masks, etc.), insufficient clear guidelines about actions to take and the duration of quarantine, the interruption of professional activities and the related financial loss (4). In this view, any strategy that aims to reduce the psychological burden of the coronavirus is extremely necessary (10). In particular, the outbreak of coronavirus is rapidly changing stakeholders’ attitudes towards e-mental health, and this should be harnessed given the fact that many technological solutions are not only cost-effective but nowadays the only possible intervention that confined individuals can receive (49). Despite the undoubted negative consequences of this context, it can be also conceived as an opportunity to achieve *an implementable revolution in digital mental health* (50).

This pragmatic pilot trial seeks to understand if and how a weekly self-help protocol—The Secret Garden—can help overcome the psychological burden of the coronavirus. To reach this goal, the protocol will use virtual reality (24) to provide a transformative experience (27, 51, 52) by offering a natural digital place in which subjects can relax and reflect. This effect will be enhanced by different daily social tasks aiming at facilitating a process of critical examination and eventually revision of core assumptions and beliefs. It is important to underline that the goal of the self-help protocol is not to provide a full structured psychological intervention, but to build the “surgical mask” of mental health support. Its goal is not to solve complex mental health problems, but rather to reduce the coronavirus of the by relieving anxiety and stress and improving interpersonal relationships: when a user is positive and healthy, he/she generates a positive social effect that contributes to the well-being of the community. If the present pragmatic pilot trial will support the feasibility of the approach, further actions to promote the dissemination and the use of the self-help protocol will be encouraged.

## Ethics Statement

The trial is approved by the Ethics Committee of the Istituto Auxologico Italiano.

